**Fig. 1 Fig1:**
[figure not shown]
Process model for user-centered digital development

### Aim 1: User-centered development of a behavioral economic-inspired CDS tool

Implementing a user-centered design process, we will incorporate behavioral economic approaches into existing CDS tools and clinical workflows to design, develop, iteratively refine, and user-test the module in two “vanguard” sites.

#### User-centered design of initial module (aim 1, phase 1)

The development and refinement process for the new BE CDS modules involves a series of linked steps that have been successfully used in previous CDS development studies [41–45]. The process includes user research, prototyping, and usability testing (see Fig. 1) [46, 47].

These processes will be used to identify or “discover” candidate BE concepts and potential CDS tools, which will then be analyzed according to their potential for workflow integration, their likely impact, and the complexity of their EHR development.

##### Identification of behavioral economic approaches and module opportunities and utilization measures

Initially, the BE and CDS literature will be further reviewed and candidate approaches selected for evaluation by the research team. Based on prior work and the current literature, Table 1 outlines example BE concepts and relevant CDS tools to support the implementation of each BE approach, along with utilization measures available to assess process outcomes.

**Table 1 Tab1:** Behavioral economic strategies and associated module opportunity examples

BE strategy	Module opportunity	Utilization measure
Suggest alternatives [48]	Alert suggests metformin when trying to prescribe other diabetes medication in CW eligible patient	Percentage of eligible alerts where alternative is selected
Accountable justification [48]	Subcomponent of alert asking for justification if prescribing diabetes medication other than metformin	Percentage of eligible alerts where justification is provided (vs. only “clicked through”)
Defaults [30, 49]	Default all diabetes management order sets to suggest metformin in eligible patients	Percentage of order sets where clinician changes the default option
Anchoring [50]	Update HbA1c lab reports for CW eligible patients to show less aggressive treatment goals	Qualitative feedback and percentage of CW compliant patients pre- and post implementation update
Peer comparisons/norming [48, 51]	Modify clinician quality and safety dashboard to visualize diabetes management peer comparisons with color codes to indicate relative performance	Number of views of the peer comparison dashboard
Availability bias [30]	Medication preference list prioritizes metformin	Number of prescriptions for metformin initiated from preference list

##### Key informant interviews

The team will conduct key informant interviews with BE, CDS, and clinical experts using a semi-structured interview guide to explore (1) the potential impact of BE principles and strategies on improving guideline adherence for diabetes management in older adults, (2) the functionality of established CDS tools amenable to implementing the BE approach, (3) the clinical workflow footprint of the BE CDS nudges, and (4) how well candidate BE CDS nudges combine into a modular package of BE CDS tools.

##### Workflow analysis

The team will also conduct a workflow analysis adapted from the Agency for Healthcare Research and Quality (AHRQ) recommendations on workflow assessments [48]. We will conduct short observations in two selected vanguard clinic locations. The literature, interviews, and workflow assessments will be used in generation of the initial prototype BE-EHR module.

Workflows will be validated in a design-thinking workshop (described below), in follow-up interviews with key informants, and within-group feedback meetings with clinicians during user testing. During these follow-up meetings, any additional workflow variations that the module may need to support will be identified. Candidate workflows will then be discussed with the project team and other health system stakeholders to finalize the optimal workflow integration approach.

##### Design workshop

After initial key informant interviews and workflow analysis, a design-thinking workshop will be held to bring together findings from the interviews and workflow analysis. The design workshop will feature a structured, multidisciplinary workgroup composed of BE experts, CDS developers, relevant clinicians, and the research team. The sessions will be guided by a user-centered design facilitation protocol that sequentially leads the group through presentation and idea generation exercises around relevant behavioral economic concepts, CDS opportunities, and workflow obstacles and opportunities. Participants will be divided into small groups and provided materials and tasks designed to prompt new thinking on potential nudges. For example, the “crazy eights” exercise is an exercise in which individual team members are directed to draw eight ideas in 8 min. Each participant will be provided opportunities to “share back” their small group’s ideas as well as provide feedback on other groups’ ideas.

The primary goal of the workshop is to prompt divergent thinking or “discovery” (see Fig. 1) where participants focus on generating as many ideas as possible, as exemplified by the crazy eights exercise. Toward the end, the facilitator directs the group to “define” or converge on the best ideas for more explicit definition and development; to this end, the workshop will complete with the whole group voting on nudge ideas believed to be most promising. The session will be video- and audio-recorded, as well as summarized and converted into recommendations and revised workflow diagrams.

#### User testing (aim 1, phase 2)

Prior studies also established a clear link between the user-centered design process and successful implementation of clinical decision support tools within the EHR [49–51]. Upon completion of the design-thinking workshop and subsequent development of nudge prototypes, nudges will be further refined through a tailored, multi-phase feedback gathering and user testing process [46]. This pre-clinical testing serves as a clinical laboratory for building successful workflow-integrated tools with a high likelihood of adoption and adherence [41, 44, 52]. In addition to key informant interviews and group interviews with users as described above, a variety of methods for collecting both qualitative as well as quantitative user feedback will be selected. See Table 2 for user research methodologies to be employed on an as needed basis according to fit based on type of module, content, frequency of clinician “exposure,” and response to the module.

**Table 2 Tab2:** Possible research methods for user testing

User testing methods	Description	Predicted frequency and time point
Key informant interviews	Semi-structured interviews with individual or small group (2–3) experts in primary care, geriatrics, EHR, diabetes, and other relevant fields	6–8 informants, 1–2 interviews each
Group interviews	Semi-structured interviews with groups of 4–6 clinicians	Pre- and post vanguard
“Ride along” observation	Individual observation session of clinician interaction with EHR real time, in situ	6–8 sessions per vanguard and pilot
Think-aloud usability testing [53]	Individual observations in “lab” of clinicians verbalizing all thoughts as they interact with the module following a carefully scripted series of EHR tasks	4–6 observations as needed in pilot
Near live [50, 53, 55]	Individual observations in “lab” of clinicians interacting with simulated data and patient actors to realistically model clinical use of module	4–6 observations as needed in pilot
Live [51, 56]	Individual observations of clinicians in situ using the tool in actual patient care	3 observations as needed in pilot

##### Development of algorithms to determine activation of CDS

In order to build a user-centered CDS tool that triggers appropriately for the target patient population, algorithms will be built-in to drive timing and content of module firings that incorporate both patient life expectancy (high, medium, low) and target glycemic index. A life expectancy algorithm (based on a scoring approach used by Quan et al. and prior research by DuGoff et al.) will be developed by the research team [53, 54]; it will be used to assign patients to low, medium, and high life expectancy categories based on patient characteristics including age, gender, and both the number and type of comorbidities. Depending on a patient’s life expectancy categorization, the individual will be assigned a target HbA1c range according to the specifications stated by the CW guideline targeting overtreatment of older patients with diabetes.

Developing an algorithm that accurately predicts life expectancy using electronic health record data poses challenges. One limitation is that the number and type of comorbidities recorded in the electronic medical record may be associated with the length of patient registration and frequency of visits. This would lead to under-reporting of comorbidities for some patients, which could lead to a higher predicted life expectancy categorization and consequential bias toward over-reporting compliance with the Choosing Wisely guidelines. While we are not able to validate the life expectancy algorithm by obtaining death certificate data, the peer-reviewed literature that we will utilize for building this algorithm is well-known and was created using data sources that verified accuracy using death certification data or sources directly applicable to analyzing EHR data. For example, Quan et al. developed a weighted scoring approach for the comorbidities using hospital and death certification data, and DuGoff et al. formulated their life expectancy tables assuming chronic conditions using Medicare beneficiary data from a sample of over 1.3 million patients [53, 54]. Therefore, we are confident that our adaptation of these algorithms will perform well in this setting.

Clinical decisions in accordance with the CW guideline will be drafted and approved by clinical experts on the research team and will guide actions prompted by text and visuals in the CDS modules. Example clinical actions include switching a patient’s medication to metformin, reducing the dose, or removing the prescription of an alternative medication for patients with an HbA1c laboratory value too tightly controlled given their calculated life expectancy. Once the new module has stabilized within the vanguard sites (workflow issues are resolved and clinician usage is stable) (aim 1), the tool will be activated at the pilot sites (aim 2).

### Aim 2: Pilot testing the BE-EHR modules (phase 3)

To assess the utilization and feasibility of the new tools and generate preliminary estimates of clinician compliance with the CW guideline, a 6-month, single-arm pilot study of the BE-EHR module will be conducted in six outpatient primary care clinics.

#### Intervention

The BE CDS module will trigger for appropriate patients according to the logic built into the module based on the patient’s age, life expectancy (as calculated by the algorithm described above), and current/target HbA1c. Based on these characteristics, the CDS may, for example, leverage the behavioral economic principle of defaults and suggest metformin if appropriate. Otherwise, the CDS will suggest not adding a new prescription if the HbA1c is above the lower bound of the target HbA1c threshold among the three life expectancy categories (7.0% for healthy patients, 7.5% for those with moderate comorbidity, and 8.0% for those with a shorter life expectancy [4, 12]). The CDS will suggest stopping or reducing the medication dose if the HbA1c is below the lower bound of the target HbA1c target threshold per life expectancy category, as that would indicate the patient’s HbA1c is being too tightly controlled. The BE CDS module (see Table 1) will be activated at the system level for all relevant diabetes EHR components. For example, a diabetes order set tailored to older adults might have default medications updated to be metformin and to reflect the CW-recommended glycemic targets for calculated life expectancy.

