### Choosing Wisely guideline for older adults with diabetes

Due to evidence that tight glycemic control in older adults with diabetes may be medically harmful, in 2013 (revised in 2015), the American Geriatrics Society (AGS) developed ten Choosing Wisely (CW) guidelines, of which the third guideline states the following: “Avoid using medications other than metformin to achieve hemoglobin HbA1c<7.5% in most older adults; moderate control is generally better.” [11] Specifically, this guideline incorporates the balance between the number of comorbidities and life expectancy of older adults to provide target ranges for glycemic goals. Reasonable targets include an HbA1c of 7.0–7.5% in healthy, older adults with long life expectancy; 7.5–8.0% for patients with moderate comorbidity and a life expectancy of less than 10 years; and 8.0–9.0% for patients with multiple comorbid conditions and a shorter life expectancy [4, 12].

These recommendations build on previous work categorizing older adults with diabetes into three clinical groups based on health status [13] and have been endorsed by numerous expert panels and guidelines [8, 14, 15]. The target ranges for glycemic control are similar to HbA1c values that have been associated with the best outcomes for older adults with comorbid conditions in observational or modeling studies [16–18]. The American Diabetes Association (ADA) and others have recommended similar health status categories related to HbA1c targets in older adults [8, 14, 15]. Although the ADA guidelines do not identify less aggressive targets for HbA1c [8], other societies, including AGS, recommend similar less aggressive thresholds for glycemic control [15, 19–21].

Despite the CW recommendations, a substantial number of older adults have intensive glycemic control that may not be necessary [22–24]. Additionally, older patients with intensive glycemic control generally do not undergo de-intensification of therapy, suggesting opportunity for improving appropriate care [25]. To combat this problem, the proposed study utilizes a unique approach: using behavioral economics via electronic health records to influence provider behavior with respect to diabetes care for older adults.

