#### Setting and population

The New York University Langone Medical Center (NYULMC) primary care practices serve patients with a diverse range of socio-demographic characteristics; they range from faculty-based practices with predominately privately insured and/or Medicare patients to Federally Qualified Healthcare Centers with a large Medicaid population (see Table 3). For the pilot study, four practices will be recruited, purposely chosen to reflect key practice setting characteristics (number of full-time providers, depth of support staff, transition to medical home model, insurance mix, patient socio-demographics).

**Table 3 Tab3:** Patient population

Primary care and endocrine practices (N)	78
Demographics	
% Black	15
% Hispanic	43
% Asian	9
% White	25
% Other	8
Patients ≥ 75 with diabetes	5187

Eligible patients within the practice sites will be those aged 76 or older with a diagnosis of diabetes. Patients will be categorized into one of the three glycemic target ranges inspired by the CW recommendation: (1) healthy older adults with an HbA1c target range of 7–7.5% and long life expectancy (defined here as 10+ years); (2) those with moderate comorbidity and a life expectancy of 3+ to 10 years, with a target range of 7.5–8%; and (3) those with multiple comorbidities and life expectancy of less than or equal to 3 years, with a target range of 8–9% [4]. These categories are determined using the life expectancy algorithm described earlier. We expect the majority of patients in the selected population to fall into the “high life expectancy” category (10+ years), as the average life expectancy of a 75-year-old is between 11 and 12 years [53], and about two thirds of patients in the Medicare population have multiple chronic conditions [54–57]. Twenty percent of the population is estimated to be moderately healthy older adults with a medium life expectancy, and 10% are estimated to have an end-stage illness, leading to low life expectancy.

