#### Outcomes

Pilot study outcomes will measure implementation as well as provide initial estimates of the BE-EHR modules’ effectiveness.

Process outcomes include utilization, measured via the EHR, such as the percentage of alerts in which the clinician changes the default option. Other outcomes are noted in Table 1. We will also collect qualitative user feedback using user research methods deemed most appropriate (see Table 2) to understand clinicians’ experience with the BE-EHR module and evaluate the specific nudges, as well as explore acceptability, implementation, and adoption issues surrounding them, including assessing their impact on guideline-focused care for older adults with diabetes.

The primary clinical outcome is the percent of eligible patients who are compliant with the AGS CW guideline targeting overtreatment of older adults with diabetes. For each patient, the HbA1c level, diabetes medication prescription status, and life expectancy status will be determined. All patients whose HbA1c are within the target range for their life expectancy status will be considered compliant. Those whose HbA1c are below the target range and who are being treated with a non-metformin agent (i.e., are over-controlled) will be deemed non-compliant. If an eligible patient is on metformin only but the HbA1c is below the upper board of the target range, they will also be deemed non-compliant. These situations are delineated in Table 4. Patient-level compliance outcomes will be aggregated to produce a provider-level compliance rate as a proportion of each provider’s eligible patients.

**Table 4 Tab4:** Choosing Wisely non-compliance categories

Measured HbA1c	Patient category	Current prescription
< 7	Healthy	Non-metformin agent
< 7	Moderate comorbidity	Non-metformin agent
< 7	Shorter life expectancy	Non-metformin agent
7–7.5	Moderate comorbidity	Non-metformin agent
7–7.5	Shorter life expectancy	Non-metformin agent
7.5–8	Shorter life expectancy	Non-metformin agent

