#### Intervention pruning

We will apply mixed methods “pruning criteria” to eliminate less effective approaches. To address the evaluation of individual components, utilization measures will be assessed to determine the value of the tool for incorporation into the eventual BE-EHR module. If the CDS tool is utilized in more than 30% of opportunities (e.g., if a suggested default is accepted in more than 30% of cases), then this tool will be retained in the module. While there is no gold standard threshold for what a “useful” CDS tool utilization rate should be, studies have noted common CDS tools with utilization rates between 5 and 40% depending on the type of CDS and the risk of ignoring it [59–61]. Furthermore, while low utilization rates may prove clinically worthwhile in high-risk patient safety situations, lower risk scenarios like the CW diabetes guidelines for older adults dictate the need for a stronger mean adoption rate [49]. Certain tools will not be evaluable with this criterion, for example, the effect of adjusting the language on HbA1c lab reports. For these tools, qualitative user feedback during usability testing and brief interviews with key informants during piloting will be used to complement the utilization pruning criterion.

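### The printed do-not-add rule has a lower HbA1c bound but no upper limit, although the protocol's targets are two-sided; the primary outcome also does not say how above-range patients are classed.

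*Protocol article*

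**What the plan says.** The Intervention section of Aim 2 gives two HbA1c rules. When metformin is not suggested, "the CDS will suggest not adding a new prescription if the HbA1c is above the lower bound of the target HbA1c threshold"; the lower bounds printed are 7.0% (healthy), 7.5% (moderate comorbidity) and 8.0% (shorter life expectancy). The next sentence covers the other side of the same cut point: "The CDS will suggest stopping or reducing the medication dose if the HbA1c is below the lower bound". Neither sentence mentions an upper bound.

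Elsewhere the targets have two ends. Setting and population lists "healthy older adults with an HbA1c target range of 7–7.5% and long life expectancy", then 7.5–8% and 8–9% for the other two categories. The Background section on the guideline gives the same ranges, for example "7.5–8.0% for patients with moderate comorbidity and a life expectancy of less than 10 years".

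For the primary clinical outcome, the Outcomes section says "All patients whose HbA1c are within the target range for their life expectancy status will be considered compliant". It then names two non-compliant groups. One is "Those whose HbA1c are below the target range and who are being treated with a non-metformin agent"; the other is patients on metformin alone whose HbA1c lies under the upper end of their range. Table 4 lists six non-compliant combinations. The Utilization rates section requires each patient to be put in one of two classes, compliant or not.

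**The concern.** The two printed rules split the HbA1c scale at a single point, the lower bound. Everything above that point receives the same advice, whether the patient is within target or well above it. The protocol's own targets support advice against adding treatment only within the range. The guideline text quoted in the Background warns against using drugs other than metformin to push HbA1c below 7.5%; it does not advise against treating a patient who is above range.

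If the module were built from this sentence as it stands, it could discourage added treatment in older adults whose HbA1c already exceeds their relaxed target. The protocol also intends other EHR users to reproduce the module, so the wording of the rule matters beyond this pilot.

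The outcome has a related gap. Above-range patients are eligible and so belong in the denominator, but no sentence says which class they fall in.

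**Working it through.** The plan gives no figure on this point to reproduce, so the check sets the printed rules against the printed targets.

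**Inputs.** Lower bounds L = 7.0, 7.5, 8.0% (Intervention). Target ranges L to U = 7–7.5, 7.5–8, 8–9% (Setting and population). Rule A: metformin not suggested and HbA1c > L, advise not adding. Rule B: HbA1c < L, advise stopping or reducing.

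**Step 1: apply the rules where metformin is not suggested.**

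| Category | Below range | Within range | Above range |
|---|---|---|---|
| Healthy | < 7.0: stop or reduce | 7.0–7.5: do not add | > 7.5: do not add |
| Moderate comorbidity | < 7.5: stop or reduce | 7.5–8.0: do not add | > 8.0: do not add |
| Shorter life expectancy | < 8.0: stop or reduce | 8.0–9.0: do not add | > 9.0: do not add |

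There are 3 × 3 = 9 cells. Rule A covers 3 within + 3 above = 6. The two-sided targets support it in the 3 within-range cells. The excess is 6 − 3 = 3, all above range. These are counts of rule cells, not of patients.

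**Step 2: one case.** A healthy patient has HbA1c 11.0% and is not offered metformin. 11.0 > 7.0, so Rule A applies, although the patient is 11.0 − 7.5 = 3.5 percentage points above the upper end of the target. No printed rule prevents this.

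**Step 3: outcome label for an above-range patient.** Within range: no. Below range on a non-metformin agent: no. Metformin alone and under the upper end: no. In Table 4, the highest HbA1c listed is 7 for healthy, 7.5 for moderate comorbidity and 8 for shorter life expectancy, which is the lower bound in each case, so no row is above range. The text assigns no label.

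**Step 4: what the classification is worth.** Let p be the share of eligible patients who are compliant leaving above-range patients aside, and u the share above range. The rate is p + u if they count as compliant and p if they do not; the difference is u. The documents give no value of u. Under an assumed 10 to 40%, the rate moves by 10 to 40 points.

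**Step 5: which class the documents point to.** The section on activation algorithms says that under-recorded comorbidity raises predicted life expectancy and so inflates reported compliance. Take a patient with moderate comorbidity at 7.7% on a non-metformin agent: within 7.5–8, hence compliant. Misclassified as healthy (7–7.5), the patient is above range. If above range were non-compliant, this error would lower reported compliance, against the stated direction. If above range is compliant, nothing changes, while a patient at 7.2% on the same treatment moves from non-compliant to compliant, as the section says. The stated direction therefore fits the reading that above-range patients are compliant.

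**The case against.** The strongest reply is that the printed sentence is not the whole logic. The same section opens with "The BE CDS module will trigger for appropriate patients according to the logic built into the module", and that logic draws on current and target HbA1c. The section on activation algorithms assigns each patient a full target range, and clinical experts must approve the actions. Vanguard sites have to stabilise before the pilot sites go live, and firing and user actions are checked in the first month. The advice can be overridden by a clinician who sees the HbA1c. All of this stands and makes a sensible build likely. None of it states the missing limit, and the rule as printed comes with numbers, so this is not merely a detail left to a fuller document.

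On the outcome, the reply is that the guideline targets overtreatment and Table 4 lists no above-range row, so these patients count as compliant by complement. That is probably the intention. It remains an inference: the text defines compliance as being within range, and Table 4 is not exhaustive, since it omits the metformin-only group that the text calls non-compliant.

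Two stronger readings are tempting, and the documents support neither. A reader might infer that the retention rule ("If the CDS tool is utilized in more than 30% of opportunities") would reward accepted do-not-add advice in above-range patients. Table 1, which gives examples, has no measure that counts acceptance of such advice, and no other section says that it will count. A reader might also infer that the compliance rate would hide or reveal resulting harm. The missing limit acts on patients already above range; if they stay there, the rate is unchanged under either classification.

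**Conclusion.** The point holds as a defect in a printed rule. Followed as written, the do-not-add advice extends to all three above-range cells, where the protocol's targets do not support it. It applies only to patients to whom metformin is not suggested. The authors probably mean within range, and the planned safeguards make a literal build unlikely. It would go too far to say that the module will discourage needed treatment: the built logic is not shown, and the number of patients affected cannot be estimated from these documents.

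The unlabelled above-range group in the primary outcome is secondary. The overtreatment aim, Table 4 and the stated direction of bias point to compliant, but the text does not say so, and the rate depends on it by exactly the above-range share. Overall the matter is minor to moderate.

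**What to change.** 1. In the Intervention section, restrict the do-not-add suggestion to HbA1c within the category's range (7.0–7.5, 7.5–8.0, 8.0–9.0%) and state that it is not shown above 7.5, 8.0 or 9.0% respectively. Leave the stop-or-reduce rule as it is.
2. Before activation, run one above-range test case per life-expectancy category and confirm that no do-not-add advice appears.
3. In the Outcomes section, add one sentence saying that above-range patients count as compliant, if that is the intention, and report their number beside the compliance rate.

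The cost is two sentences, three test cases and one extra count. No new data are needed, because HbA1c, prescription status and life-expectancy status are already to be determined for every patient.
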